# Promoting parenting strategies to improve tooth brushing in children: design of a non-randomised cluster-controlled trial

**DOI:** 10.1186/s12903-019-0902-6

**Published:** 2019-09-06

**Keywords:** Dental caries, Prevention, Intervention, Parenting, Tooth brushing, Self-efficacy

## Abstract

**Background:**

Tooth brushing with fluoride toothpaste is a key recommendation in evidence-based guidelines for caries prevention. Parents generally have sufficient knowledge to practice tooth brushing for their child, yet many experience barriers to actually implement the behaviour. Common barriers are associated with difficult child behaviour, stress, poor family organisation and management of routines. These underlying determinants of tooth brushing behaviour should be addressed in caries-preventive interventions.

The ‘Uitblinkers’ intervention is a semi-structured interview method developed for oral healthcare professionals (OHPs), with the aim to improve the practice of twice daily tooth brushing in children. The interview method focusses on ^1)^ identifying parents’ barriers to tooth brushing, and ^2)^ promoting parenting strategies (related to tooth brushing) to tackle the identified barriers. The intervention applies principles from learning theory, including stimulus control, operant conditioning and authoritative parenting. This paper describes a study protocol to evaluate the effect of the intervention.

**Methods:**

This non-randomised cluster-controlled trial will be conducted in 40 general dental practices in The Netherlands. Intervention practices will implement the intervention in addition to care as usual, while control practices will only provide care as usual. From each dental practice, a random sample of 3 to 4-year-old children will be recruited. The intervention consists of three sessions between an OHP and parent, in which parenting strategies for identified barriers are discussed. The primary study outcome is children’s dental caries experience after 24 months. Secondary outcomes include parents’ self-efficacy in brushing their children’s teeth, tooth brushing frequency in children and children’s dental plaque scores. Differences in outcomes between the intervention and control group will be assessed using logistic and negative binomial regression. The feasibility of the intervention will be assessed through process evaluation.

**Discussion:**

Findings of this study will ascertain whether promoting parenting strategies is a successful method to improve tooth brushing in children and to prevent childhood dental caries in a clinical dental setting.

**Trial registration:**

This trial is registered with the Netherlands National Trial Register (registration date: 7 September 2018; trial registration number: NTR7469).

**Electronic supplementary material:**

The online version of this article (10.1186/s12903-019-0902-6) contains supplementary material, which is available to authorized users.

## Background

The prevention of tooth decay in children seems fairly straightforward. The disease can largely be prevented by the use of fluorides, good oral hygiene and a non-cariogenic diet. There is overwhelming evidence that long-term exposure to low concentrations of fluoride is associated with a clear reduction in dental caries [1]. According to the World Health Organization (WHO), fluoride toothpaste is the most widespread and accepted form of fluoride use globally, and the most realistic and effective means to reduce the burden of tooth decay in populations [2]. Hence, twice daily tooth brushing with fluoride toothpaste by the parent as soon as the first primary teeth erupt is one of the key messages in evidence-based guidelines for caries prevention, including those of Public Health England [3] and the Dutch Ivory Cross [4].

The challenge however, lies in achieving personal compliance with this message. The conventional method to improve children’s oral hygiene, i.e. through dental health education and awareness raising, rarely leads to the intended behaviour change [5]. Systematic reviews confirmed the limited effectiveness of a purely educative approach in producing long-term oral hygiene improvements [6, 7], particularly when it is solely focussed on knowledge provision and tooth brushing instructions. Knowledge and technical skills are *necessary*, but seldom *sufficient* for sustained oral hygiene behaviour change.

Guidelines recommend that parents brush their children’s teeth and supervise tooth brushing until children are 10 years old [4]. Qualitative research with parents revealed that almost all parents recognize the importance of twice daily tooth brushing for their child [8, 9]. However, many parents reported barriers to actually adhere to the advice. Non-compliant child behaviour was often due to tantrums, pain during teething or tiredness of the child. Some parents avoided conflict in those situations than to persist on tooth brushing, which often meant engaging in very lively debates with their child. Other parents reported challenges with tooth brushing due to time constraints, a busy schedule or feelings of stress or fatigue. These findings highlight that simple behaviours such as tooth brushing are enmeshed in more complex daily habits, which are influenced by a range of child, parental and family-related factors.

Naturally, regular tooth brushing is more likely to be practiced in a supportive and organised home environment, where roles and boundaries are well-defined and routines are managed. Duijster et al. [10] showed that children from families that lack structure and routines are at higher risk of developing dental caries. In addition, Abegg et al. [11] demonstrated that a certain extent of flexibility is important to ensure regular tooth brushing. Furthermore, parenting practices influence how behavioural directions of the parent are delivered to and accepted by the child. Ineffective parenting, characterised by inconsistent and highly demanding discipline practices, evokes more resistance and non-compliance in children [12, 13]. This may also negatively affect children’s compliance towards twice daily tooth brushing. Effective parenting on the other hand, in terms of positive involvement (nurturance and sensitivity), positive reinforcement (encouragement and compliments) and problem-solving, has been associated with better oral hygiene and lower levels of dental caries in children [14–17].

In summary, many barriers to twice daily tooth brushing seem to revolve around the family environment. In this context, efforts to improve children’s oral hygiene should not narrowly focus on knowledge provision alone. Efforts should focus on the underlying determinants of twice daily tooth brushing and incorporate components of interventions that target parenting and broader family behaviour.

### The ‘Uitblinkers’ intervention

In 2017, the ‘Uitblinkers’ intervention (translation: brilliant stars) has been developed. The aim of this intervention is to improve the practice of twice daily tooth brushing in children to prevent dental caries on the long-term. The intervention is a semi-structured interview method primarily developed for a dental setting, targeting parents of 2 to 10-year-old children. The intervention focusses on identifying barriers that parents experience with brushing their children’s teeth, and promoting parenting strategies (related to tooth brushing) to tackle the identified barriers, using principles from learning theory. The hypothesis of the intervention is that the promotion of specific parenting strategies will increase parents’ self-efficacy (confidence) in brushing their children’s teeth when experiencing barriers, which in turn will lead to the improved practice of twice daily tooth brushing with fluoride toothpaste in children and reductions in children’s dental plaque scores. This is hypothesised to subsequently result in lower development of childhood dental caries. Figure 1 shows the components and hypothesised outcomes of the intervention.

**Fig. 1 Fig1:**
[figure not shown]
Components and hypothesised outcomes of the ‘Uitblinkers’ intervention

#### Underlying theory – principles from learning theory

Principles from learning theory are applied to promote specific parenting strategies related to tooth brushing, with particular emphasis on stimulus control and operant conditioning. Stimulus control and operant conditioning are concepts from behavioural psychology, which argue that new behaviours or changes in behaviour are acquired through repetitive associations between stimuli and response [18].

Stimulus control refers to controlling stimuli before a behaviour occurs. Parenting skills related to stimulus control concentrate on enabling parents to create the conditions that stimulate, rather than hinder, desired behaviour in the child. This is done through structuring time and space, introducing ground rules and predictable routines, and through managing children’s problem behaviour by setting boundaries, giving clear instructions and the use of consistent measures [19].

Operant conditioning focusses on the relationship between a behaviour and its consequences. Operant conditioning can be defined as a learning process by which behaviours are modified by either (intermittent) reinforcement or a form of punishment [20, 21]. Parenting skills related to operant conditioning focus on teaching parents to positively reinforce desired behaviours of the child, e.g. through praise and reward. This will increase the likelihood that the child continues to show the desired behaviour. Undesired child behaviours should be decreased by ignoring the behaviour, which promotes extinction, or in some cases through punishment. Punishment could take several forms, including adding a negative stimulus (e.g. spanking), or removal of a positive stimulus (e.g. taking away a child’s toy). In child education, the use of the latter is being encouraged.

In addition to principles of stimulus control and operant conditioning, the intervention stimulates an authoritative parenting style, characterised by expression of warmth and sensitivity, and the use of clear communication about behavioural boundaries and expectations [22].

### Aim of the study

A study will be conducted to evaluate the ‘Uitblinkers’ intervention. The aim of the study is to assess the effect of the intervention on children’s dental caries experience after 24 months and on tooth brushing-related outcomes, including ^1)^ parents’ self-efficacy in brushing their children’s teeth, ^2)^ tooth brushing frequency in children and ^3)^ children’s dental plaque scores. A second objective is to conduct a process evaluation to assess the feasibility of the intervention, as well as oral healthcare professional’s (OPHs) and parents’ perceptions of the intervention. This paper describes the ‘Uitblinkers’ intervention and sets out the design of the study.

## Methods

### Design and study setting

The study is designed as a non-randomised cluster-controlled trial with a duration of 24 months. The study will be conducted in general dental practices located in The Netherlands. The medical ethical committee of the Vrije Universiteit in the Netherlands has provided ethical approval for this study (no. 17397).

### Study sample

#### General dental practices

The study will include 40 general dental practices: 20 practices in the intervention group and 20 in the control group. A convenience sampling method will be used to recruit dental practices for the intervention group. OHPs will be informed about the study at dental conferences and in-service training in The Netherlands, after which they are encouraged to voluntarily apply for participation. Practices will be eligible to participate if they have employed a certified dental therapist who is able to carry out and coordinate the study within their practice. Referral practices for paediatric dental care will be excluded from participation. All practices that apply will receive an information letter describing the procedures of the study, after which they will be asked to confirm their participation. Practices in both rural and urban regions will be included in the study.

For each participating dental practice in the intervention group, a matching control practice will be selected based on two factors: similar size of the patient population, with a maximum deviation in size of 500 registered patients; and same socioeconomic status (SES) of the region, as classified by the Dutch Central Bureau of Statistics on a scale from 1 (lowest SES) to 7 (highest SES) [23]. The size of the patient population gives an indication of the characteristics of a dental practice (e.g. solo or large group practice), and the SES of the region is indicative of the population’s (oral) health, with higher caries levels being reported in low SES regions [24]. Selected practices will be approached by e-mail, containing the information letter, and by telephone. As an incentive for participation, control practices will be offered training in the intervention method after the study is completed.

#### Children and their parent(s)

Each dental practice, both in the intervention and control group, will recruit a sample of at least ten 3 to 4-year-old children from their own patient population for inclusion in the study, using a simple random sampling method. Eligible children will be listed from the patient registry and given a random number by the coordinating dental therapist, using the website http://random.org. Subjects will be approached in numerical order until at least ten subjects are included. In cases of twins, only one child of the family will be selected. Children will be eligible to participate if they are healthy (ASA classification I) and between 36 and 59 months old at the time of inclusion. Exclusion criteria are:
Children with a physical or mental disability,Children with a high caries activity (decayed, missing and filled teeth (dmft) ≥ 4), based on the patient dental record,Children with hypomineralised second primary molars,Children (or siblings of the child) who have been receiving treatment at a referral practice for paediatric dental care,Children of parents who do not speak and understand the Dutch language.

Three to 4-year-olds are selected for two reasons. First, the restriction of the age group reduces variation in dental caries levels, allowing better comparison of the intervention’s effect. Second, children are preferably targeted from a young age when oral health behaviours are still shaped and more amendable to change. However, in The Netherlands only 35% of two-year-olds are visiting the dentist, which increases to 95% when children reach the age of four [25]. Therefore, the choice was made to include 3 to 4-year-old children, increasing the number of young children that can be reached. Parents will be informed about the study aim and procedures, privacy and confidentiality regulations and their rights to withdraw at any time using an information letter (Additional file 1). Prior to participation, written informed consent will be obtained from the parents by the dental therapist.

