#### Measures of fidelity

Fidelity is defined as the extent to which delivery of an intervention adheres to the protocol originally developed [38]. To measure fidelity, dental therapists in the intervention group will be requested to document the selected barriers and action points of participants. Questions on the implementation of the intervention are included in the questionnaire and focus group interview with dental therapists (see Additional files 2 and 3). In addition, the 20 parents who will be contacted for a telephone interview will be asked to give a description of their research visit, to determine whether the study protocol was followed as intended.

To assess whether the target group is reached, dental therapists in both intervention and control practices will be requested to document the number of subjects that agreed to participate out of the number of eligible subjects that were approached, as well as reasons not to participate. Non-participating parents will be asked two questions on their highest completed level of education and country of birth, to be able to assess potential selection bias.

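### The practice's own unblinded therapist lists and numbers the children after the arm is known, and the recruitment log cannot show who was left off or skipped

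*Protocol article*

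**What the plan says.** Allocation is by practice and not random: "The study is designed as a non-randomised cluster-controlled trial with a duration of 24 months". Intervention practices volunteer ("A convenience sampling method will be used to recruit dental practices for the intervention group"), and controls are then found for them: "For each participating dental practice in the intervention group, a matching control practice will be selected based on two factors". To take part, a practice must employ a "certified dental therapist who is able to carry out and coordinate the study within their practice".

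Recruitment of children comes after this. The section *Children and their parent(s)* has practices recruit once they belong to an arm: "Each dental practice, both in the intervention and control group, will recruit a sample of at least ten 3 to 4-year-old children". The draw is local: "Eligible children will be listed from the patient registry and given a random number by the coordinating dental therapist, using the website http://random.org". Then: "Subjects will be approached in numerical order until at least ten subjects are included". The same section has the dental therapist obtain written consent.

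*Training of oral healthcare professionals* trains the intervention practices' dental therapists in the interview method. *Blinding* states that participants, and professionals who provide the intervention or collect data, cannot be blinded.

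The safeguards are in two places. *Measures of fidelity* has therapists in both arms record how many approached eligible subjects agreed and why others declined, and adds: "Non-participating parents will be asked two questions on their highest completed level of education and country of birth". *Statistical analysis* takes baseline dmft differences into account and adjusts for other covariates that differ significantly at baseline.

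**The concern.** In a cluster design where the arm is known before individuals enter, the selection of individuals is a second route to imbalance, separate from the selection of clusters. Random sampling within the practice should close that route. It does so only if the person who benefits from discretion cannot exercise it. Here one unblinded role compiles the list, generates the numbers and takes consent, and no step outside the practice fixes or checks the order.

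The arms also differ in what is asked of families. *Contact moments* gives intervention parents an extra visit and a telephone recall, while control parents attend only for data collection. A therapist who has to arrange those contacts could have a reason, absent in control practices, to prefer some families over others.

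At stake is the comparability of the two groups at entry. *Outcome measures* judges success by a 25% lower caries experience, so a difference created at enrolment would feed directly into that decision.

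**Working it through.** The document gives no figure for this point, so the main check is a trace of who acts, when, and with what knowledge.

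1. **Arm before list.** Intervention practices apply, and controls are matched to practices already participating. Control practices are offered training after the study as an incentive, so they know their own arm too. Children are then recruited by practices already in one arm or the other.
2. **Who lists and numbers.** The coordinating dental therapist assigns the numbers and, on the natural reading, draws up the list. That the therapist also makes the approach is an inference from the consent step and the log, because the approach is described in the passive.
3. **What comes before numbering.** Only eligible children are listed, so exclusions are applied first. Age, recorded dmft and referral history are matters of record. ASA class I and whether the parents speak and understand Dutch leave more room for judgement.
4. **What the log captures.** Its denominator is eligible subjects who were approached. A child judged ineligible before numbering, omitted from the list or skipped in the order does not appear. The two questions to non-participants have the same boundary and do not cover motivation or caries.
5. **What adjustment captures.** Baseline dmft is used, but within the range below 4 that the exclusion criteria leave. *Co-variates* lists sociodemographic factors and other oral health behaviours such as diet, but not parental motivation.

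**Scale only, under assumptions the document does not supply.** Take the 6-year-old mean of 6.9 dmfs from *Power calculation*. The success margin is 0.25 × 6.9 = 1.725 dmfs. Assume a share s of would-be enrolees has 1.5 times the mean dmfs of the rest, and a fraction f of that share is passed over in intervention practices only. Then:

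- mean of the rest: L = 6.9 / (1 + 0.5s)
- remaining share: s′ = s(1 − f) / (1 − sf)
- enrolled mean: L(1 + 0.5s′)

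| s | f | Enrolled mean | Fall in dmfs | Share of 1.725 |
|---|---|---|---|---|
| 10% | 1 in 10 | 6.87 | 0.03 | 2% |
| 50% | 1 in 10 | 6.83 | 0.07 | 4% |
| 10% | 2 in 10 | 6.84 | 0.06 | 3% |
| 50% | 2 in 10 | 6.75 | 0.15 | 9% |
| 10% | all | 6.57 | 0.33 | 19% |
| 20% | all | 6.27 | 0.63 | 36% |

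All rows are before baseline adjustment. They also start from a general-population mean, although children with dmft of 4 or more are excluded from this study.

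**The case against.** The strongest reply is that the plan already has layers of protection. Numbers are random, the order of approach is prescribed, therapists in both arms log agreement and reasons for refusal, most exclusions are record-based, and baseline dmft enters the analysis. The design is openly non-randomised, and *Discussion* concedes selection bias from recruiting practices and a general tilt towards motivated families. Nothing suggests that draws would be repeated or children skipped. Much of this stands, and it limits the weight of the point. It does not answer the gap before the approach, where the log is silent, and the concession in *Discussion* does not cover children being enrolled differently in the two arms.

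Four stronger readings are tempting, and the document does not support them.

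- A reader might infer that local random numbering is the only safeguard. The log and the baseline adjustment show otherwise.
- A reader might infer that selection lowers caries in the intervention arm. *Development and procedure of the intervention* excludes parents who can name no barrier. That can arise only at the interview, and it could remove easy-brushing families from that arm and pull the other way. A therapist might also favour families thought to need help, and control therapists are equally unblinded.
- A reader might take the open-ended minimum of ten as a bias. Further children taken in numerical order remain a random sample.
- A reader might take a fifth to a third of the success margin as the expected bias. Those figures need every family in the higher-caries group to be dropped. Partial skipping under the same ratio gives 2% to 9%.

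**Conclusion.** The point holds as a weakness in a stated procedure. Children are listed, judged eligible and numbered inside the practice, by an unblinded therapist, after the arm is known, and omissions before the approach cannot be detected. Differential enrolment is possible, not shown. Its direction is open and its size unknown: the illustration runs from 0.03 to 0.63 dmfs according to assumptions about prevalence, caries ratio and skipping that the document does not give, and adjustment for baseline dmft would reduce it. Two steps in the chain are inferences: that the coordinating therapist personally approaches families, and that this same individual conducts the interviews. The change is a cheap improvement to make before recruitment, not a reason to doubt the design as a whole.

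**What to change.** - **List.** On a fixed date each practice lists all registered children aged 36 to 59 months, sorted by a rule set in advance. Record-based exclusions and their reasons are marked before any numbering, and the list is kept unchanged.
- **Order.** The practice sends the research team only the anonymous line count, or a pseudonymised list if the ethics approval permits. The team draws and returns the random order, with a target number set by the same rule in both arms.
- **Log.** The therapist approaches strictly in that order. The existing log is extended to one line with a reason for every number not enrolled, and these are compared by arm.
- **Limitation.** State that central ordering does not remove differences in consent once the arm is known.

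The cost is a short delay before recruitment and a small administrative load across 40 practices. Sending line counts alone avoids exporting registry data on children whose parents have not consented.
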